**Fig. 2 Fig2:**
[figure not shown]
Timeline of the BOOST pACP program with adolescents that have cancer and their parents

External facilitators will be hired by the research team to deliver the BOOST pACP program. These facilitators will receive a 2.5-day training, partly provided by a communication expert from an external firm (Wilde Kastanje Training and Education, the Netherlands) in performing ACP conversations with the adolescent and parent(s) separately and with the family members together. The facilitators meet the following criteria: Master’s degree in Psychology, advanced communication skills, and experience in working with adolescents.

#### Control

The control group will not receive the BOOST pACP program. Adolescents in the hospitals are seen by different oncologists and nurses. Families that are recruited via four participating university hospitals will have access to contact with psychologists whenever they request it. Paediatric ACP is not implemented as standard care within these hospitals. The conversation cards that can be used as a game of quartet at home are offered to the families in the control group after study completion.

#### Criteria for discontinuing or modifying allocated interventions

Families can withdraw from the study at any moment. Where a participant experiences psychological distress the facilitator, being an experienced psychologist by background, will discuss their feelings and ask if they want to continue. In addition, if a participant displays signs of psychological distress, the ACP facilitator will discuss and facilitate contact with the psychologist from the involved paediatric oncology wards. Where patients are recruited through support organizations, the facilitator will ask the family which psychologist from their facility they can contact.

A bereavement protocol will be in place for when a patient or parent dies during the study period. When the data collector is notified about the death of a participant, he/she will then notify the trial manager and ACP facilitator. The bereaved participant will receive a phone call from the data collector outlining condolences and where they can access support if required. Bereaved participants will not be asked or expected to complete follow-up study questionnaires.

#### Strategies to improve adherence to the intervention protocols

The research team also developed an implementation protocol outlining all intervention components and associated procedures, in collaboration with the facilitators that they use throughout the delivery of the BOOST pACP program. Next to the 2.5-day training, the ACP facilitators will participate in 4-monthly (or more, depending on need) intervisions/comeback sessions (‘coaching on the job’) with a researcher ([name]) and a specialist trainer (in communication) from the research group. Intervisions are aimed at providing facilitators with additional knowledge and skills required to successfully implement the program, based on a discussion of the challenges they experience, and implementation approaches and strategies to deal with these challenges.

#### Relevant concomitant care and interventions that are permitted or prohibited during the trial

There are no restrictions regarding concomitant care or interventions during the trial.

### Outcomes

Outcomes are measured at baseline (T0), 3 months after baseline (T1), and at 7 months (T2) in three groups: adolescents, parents and paediatric oncologists. The outcome measures used for the primary and secondary endpoints are shown in Table 3.

**Table 3 Tab3:** Outcome measures of the primary and secondary endpoints of the BOOST pACP program

Outcomes	Measurement instrument	No. of items	Unit of analysis	Timepoint		
				T0	T1	T2
**Primary endpoint**						
1. Quality of Parent-Adolescent Communication	Parent-Adolescent Communication Scale (PACS) [32]	20 items	Adolescent		x	
**Secondary endpoints**						
2. Quality of Parent-Adolescent Communication	PACS	20 items	Adolescent	x		x
3. Attitude on talking with the other (parent(s)/ their child) about what the adolescent finds important regarding his/her care and treatment	Created by the research team^a^	8 items	Adolescent	x	x	x
		7 items	Parent(s)	x	x	x
4. Self-efficacy towards talking with the other (parent(s)/ their child) about different ACP themes	Created by the research team^a^	9 items	Adolescent	x	x	x
4a. if the child initiates the conversation	Created by the research team^a^	9 items	Parent(s)	x	x	x
4b. to initiate the conversation his/herself	Created by the research team^a^	9 items	Parent(s)	x	x	x
5. Self-efficacy towards talking with their child and letting their child talk in different situations	Created by the research team^a^	6 items	Parent(s)	x	x	x
6. Behaviour: talking with the other (parent(s)/ their child) about different ACP themes	Created by the research team^a^	9 items	Adolescent	x	x	x
		9 items	Parent(s)	x	x	x
7. Intention to talk with the other (parent(s)/ their child) parent(s) about different ACP themes	Created by the research team^a^	9 items	Adolescent	x	x	x
		9 items	Parent(s)	x	x	x
8. Behaviour: talking with paediatric oncologist about different ACP themes	Created by the research team^a^	9 items	Adolescent	x	x	x
9. Intention to talk with paediatric oncologist about different ACP themes	Created by the research team^a^	9 items	Adolescent	x	x	x
10. Anxiety	PROMIS Anxiety 8a Short version [33]^b^	8 items	Adolescent	x	x	x
	PROMIS 7a Short version [34]^b^	7 items	Parent(s)	x	x	x
11. Level of shared decision making	CollaboRATE Scale [35, 36]^c^	3 items	Parent(s)	x	x	x
12. Satisfaction items for the intervention group	Created by the research team	14 items	Adolescent and parent(s)		x	x
13. Behaviour & intention to discuss ACP with the family	Created by the research team	3 items	Oncologist	x	x	x
14. Quality of Life	EQ-5D-Y [37]	6 items	Adolescent	x	x	x
**Background characteristics**						
15. Demographic and background information	Created by the research team	3 items	Adolescent	x		
		14 items	Parent(s)	x		
16. Disease & treatment information about adolescent	Created by the research team	7–10 items	Oncologist	x	x	x

^a^The following procedure was followed: 1) The Theory of Planned Behaviour instructed ways items were formulated regarding the four key constructs operationalizing ACP as a health behaviour: attitude, self-efficacy, intention and actual behaviour; 2) the prototype instrument was linguistically improved and made age appropriate by a literacy expert agency; 3) cognitive interviews with adolescents who were diagnosed with cancer (*n =* 4) and parents (*n =* 6) were then performed; 4) feedback using thematic analysis and discussions with the researchers informed refinements. Response categories: ‘Strongly Disagree’, ‘Disagree’, ‘Neither Agree Nor Disagree’, ‘Agree’ or ‘Strongly Agree’

^b^Response categories: ‘Never’, ‘Rarely’, ‘Sometimes’, ‘Often’, or ‘Always’.

^c^Response categories: 10 – point Likert scale, ranging from ‘No effort was made’ (=0) to ‘Every effort was made’ (=10)

The full questionnaires used at T0 in these three groups are provided in Additional file 1.

#### Primary endpoint

The primary endpoint is dyadic ACP communication (between adolescent and parent) at 3 months (T1), using the Parent-Adolescent Communication Scale (PACS) [38], a validated questionnaire to measure the adolescent’s perception of their communication, as applied to pACP themes with (both of) the parent(s). The Parent-Adolescent Communication Scale [38] entails two subscales: 1) openness in communication subscale; 2) problems in communication subscale, including 20 items, that can be rated from 1 to 5 and produce factor-derived scores (range: 10–50). Items are summed for each scale, so that higher scores indicate more openness and more problems. The scores for items on the Problems subscale are reversed in value. The score ranges from 20 to 100 on the full scale. Both subscales have demonstrated strong internal consistency (alpha = 0.87–0.78) and test-retest reliability (r = 0.78–0.77) [37]. The questionnaire was translated to Dutch following a forward-backward translation procedure, in collaboration with an independent translation agency. The adolescent will fill out the PACS about both parents, if applicable.

#### Secondary endpoints

One of the secondary endpoints is dyadic communication (between adolescent and parent(s) at 7 months (T2). The other secondary endpoints will be measured at baseline (T0), T1 and T2 and include:
adolescent’s/parents’ attitudes to talking about ACP themes with his/her parent(s)/child (self-developed items)adolescent’s/parents’ self-efficacy towards talking about ACP themes with his/her parent(s)/child (self-developed items)parents’ self-efficacy towards talking with their child and letting their child talk in different situations (self-developed items)adolescent’s/parents’ behaviour of talking about ACP themes with his/her parent(s)/child (self-developed items)adolescent’s/parents’ intention to talk about ACP themes with his/her parent(s)/child (self-developed items)adolescent’s behaviour of talking about ACP themes with his/her paediatric oncologist (self-developed items)adolescent’s intention to talk about ACP themes with his/her paediatric oncologist (self-developed items)adolescent’s quality of life (EQ-5D-Y [34])parents’ perception of shared decision making in the last clinical encounter (CollaboRATE Scale [33, 36])adolescent’s/parents’ level of anxiety in the past week (PROMIS Anxiety [34, 39])paediatric oncologists’ behaviour of talking about ACP themes with the family (self-developed items)paediatric oncologists’ intention to talk about ACP themes with the family (self-developed items).

#### Participant characteristics

We will collect demographic and relevant background information from adolescents (i.e. gender, data and country of birth) and from parents (i.e. gender, date of birth, highest education). From paediatric oncologists, we will gather relevant clinical information about the adolescent (i.e. main diagnosis, recurrence, metastasis and type and line of treatment).

#### Process evaluation

Via a mixed-methods process evaluation in the intervention group, we will assess:
implementation: the structures, processes and resources through which delivery is achieved, and the quantity and quality of what is delivered [26]. Outcomes involve: a description of how the program activities were implemented, resources and dose, reach, fidelity, adaptations and quality.mechanisms of impact: the intermediate mechanisms through which program activities produce intended (or unintended) effects, and how activities, and participants’ interactions with them, trigger change [26]. Outcomes involved are responses and interactions with the program, mediators and unanticipated pathways or consequences.context: factors external to the program which may influence its implementation, or whether its mechanisms of impact act as intended, and how external factors influence the delivery and functioning of the program [26]. This involves contextual moderators and intention for maintenance.

Additional file 2 provides an overview of all process indicators that are evaluated in the process evaluation, indicating the methods applied and at what time point.

### Participant timeline

The full trial participation of participants takes up to 7 months (from baseline to filling out the last questionnaire). The flow diagram of measurements is provided in Fig. 3 and the intervention participant timeline is provided in Fig. 2.

**Fig. 3 Fig3:**
[figure not shown]
Flow diagram of adolescent and parent recruitment, randomization and measurements

### Sample size

We consider demonstration of an intervention effect on the primary endpoint as a success. The primary endpoint is the score for the Parent-Adolescent Communication Scale (PACS) [38] at 3 months (T1).

To detect a minimal relevant difference between intervention and control group at T1 of 7 with a pooled standard deviation in both groups of 11.4, with alpha at 0.05 and 80% power (1-β = 0.80), a sample of *n* = 43 is needed in each arm. Based on the experiences with the FACE intervention [40], we anticipate a 90% retention rate, similar to the FACE intervention, resulting in an estimation of 96 families in total to be enrolled.

Two other studies found a smaller difference in PACS scores between the intervention and control group (e.g. 2.57 [41] and 2.21 [42]). However, both of these intervention studies entailed minimal in-person contact and sending prompts to the parents by mobile phone. The components of the BOOST pACP program entail intensive in-person contact moments, specifically targeted at behavioural constructs to improve parent-adolescent communication on ACP themes. Therefore, we expect to see a larger effect on the PACS scale, compared with the interventions described above.

### Recruitment procedures

The recruitment period will be 2 years (2021–2023). We will recruit adolescents via two different streams:
Patients will be recruited in all four participating university hospitals in Flanders, Belgium, via the paediatric oncology wards. Each of the hospital wards will assign one staff member as the main point of contact for the study. The contact person asks each paediatric oncologist to assess which patients would meet the inclusion criteria. The paediatric oncologist or psychologist will ask the parents of these patients whether they would be willing to participate in the study by giving a short explanation and asking whether they agree for a data collector to call them to provide more information about the study. The data collector will then contact one of the parents by phone. If the parent agrees to participate, the data collector will make an appointment with the parent(s) (depending on which parents are considered eligible, see Fig. 1) and the adolescent. During the appointment, the data collector will explain that both parents are encouraged to join the conversation sessions, but that it is not obligatory for both parents to join all conversation sessions of the program to be able to enrol in the study.We will recruit adolescents with cancer and their parent(s) through support organizations that meet the following criteria: 1) they are non-profit; 2) they are based in Flanders or Brussels; 3) adolescents with cancer or their parents are one of their target groups. Organizations are contacted by the researcher ([name]) and are asked to post an open call using a flyer developed by the research team via their newsletters, website and other social media or share this in other ways that are part of their regular channels of communication with their members and network. Adolescents and/or parents can contact the data collectors (via phone or e-mail) when they are interested in participation in the study or when they have additional questions. Subsequent recruitment procedures are similar to the first recruitment stream.

### Allocation

Randomization will be performed after at least one of the parents has completed the baseline measurement. Block randomization with a 1:1 allocation ratio to either the intervention arm or the control arm will be performed, using a concealed envelope method. To ensure equal allocation of subgroups, we will stratify the allocation by age (10–14 years old vs 15–18 years old). We have opted for these age strata, because the cognitive development of adolescents between 10 and 14 years differs from those between 15 and 18 years [43, 44] which might influence the way they are able to talk about their care and treatment.Allocation concealment will be ensured, as the randomization service will not release the randomization code until the adolescent has been recruited into the trial, which takes place after all baseline measurements have been completed. After randomization, the data collector will then inform the families of their allocation to one of the study arms.

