## Methods

### Study design

A multi-centre parallel-group randomised controlled superiority trial [25] (RCT) with embedded mixed-methods process evaluation, comparing the BOOST pACP program to standard care (control group). Adolescent patients and their parent(s) will be randomised with a 1:1 allocation ratio to the intervention arm or the control arm after baseline assessment. The mixed-methods process evaluation is structured according to the Medical Research Council (MRC) Framework by Moore et al. [26].

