A maximum of two of the most involved parents will be invited to take part; the term “parent/s” includes legal guardians and stepparents. To determine which parents are to be invited into the study, data collectors will follow a flow diagram (Fig. 1). In case there is only one parent, he/she will automatically be included. If there are more than two parents in the adolescent’s life (e.g. due to blended families), the two parents with the most prominent role in raising and caring for the child will be invited to take part in the study. If the latter is difficult to determine, the most prominent parent will decide which second parent will be invited to participate in the study. The most prominent parent is the one that is usually present and accompanies the adolescent to the hospital and during oncology care and treatment, and also identifies himself or herself as the most prominent parent.

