### Data collection procedures

Quantitative data is collected at baseline (T0), after 3 months (T1), and after 7 months (T2) (see Fig. 3), using self-reported questionnaires that are pseudonymized using individual identifier codes attributed by the data collector. During a home visit, the data collector will gather written consent from both parents and written assent from the adolescent, immediately after which the baseline questionnaire is provided to the participant (paper-pencil or online using ‘LimeSurvey’, depending on the choice of the participant). The data collector will fill out the questionnaire together with the adolescent in an interview format. This will be done in a separate room from the parent(s), to avoid that the adolescent is being influenced by their presence. Parent(s) can either choose to fill out their questionnaire independently at the same time or later. The paediatric oncologist mentioned by the family as the one with whom they have most contact about care and treatment will receive a baseline questionnaire about the adolescent via an e-mail link. The data collector will send out one reminder to the parents and paediatric oncologist after 1 week. Data collection procedures are repeated at T1. At T2, questionnaires are sent to parents and adolescents, either online or via postal mail. To reduce loss to follow-up, improve retention, and encourage adolescents to fill out the questionnaires, retention gifts will be provided after completion of each data collection, at T0, T1 and T2.

Data collection procedures for the process evaluation (Additional file 2), include:
structured diary filled out by facilitators: the facilitators keep track of all activities they perform regarding the BOOST pACP program by filling out a structured diary, including multiple choice and open-ended questions, after each BOOST pACP conversation session. The diary will be completed in a Word template and will be stored in a secure folder.semi-structured individual interviews with facilitators; both facilitators will be interviewed for 60 min by a researcher at 6 months, 12 months, 18 months and after the end of the data collection period at 24 months.semi-structured individual interviews with a variety of involved paediatric oncology teams after 12 months and after study completion, at 24 months.each BOOST pACP conversation is recorded by audio (after informed consent of participants).

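### The Allocation section gives two randomisation triggers; one lets a second parent's baseline be answered after the arm is known and then used as covariate for the parent secondary endpoints

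*Protocol article*

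**What the plan says.** All references are to the protocol article.

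- **Allocation, opening sentence:** "Randomization will be performed after at least one of the parents has completed the baseline measurement".
- **Allocation, closing lines:** the code is held back until the adolescent is recruited, "which takes place after all baseline measurements have been completed". Then: "After randomization, the data collector will then inform the families of their allocation to one of the study arms".
- **Study design:** families are allocated to "the intervention arm or the control arm after baseline assessment", without saying whose assessment is meant.
- **Study setting and population:** "A maximum of two of the most involved parents will be invited to take part".
- **Data collection procedures:** the adolescent's questionnaire is completed with the data collector, by interview, at the visit where consent and assent are taken. For parents, "Parent(s) can either choose to fill out their questionnaire independently at the same time or later". The oncologist answers through an e-mail link. Parents and oncologist get one reminder after 1 week.
- **Table 2:** data collectors give the preparation booklets to intervention families, and the intervention period is counted from their receipt.
- **Data analysis and Secondary hypotheses testing:** comparisons at T1 and T2 adjust for the baseline score, and parents are analysed as a population of their own. Table 3 lists parent attitude, self-efficacy, behaviour, intention, anxiety and shared decision making, all measured at T0.

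**The concern.** Adjusting for a baseline score is safe because allocation cannot have influenced it. The Secondary hypotheses testing section relies on this when it says that the baseline predictor controls differences that existed beforehand. A T0 answered by a parent who already knows the arm, or has already opened a booklet designed to start reflection on the same themes, may carry a reaction to allocation or an early part of the effect. Adjustment then subtracts that part from the estimated difference between arms. If late answers move in the direction of benefit, the parent effect is understated; if they move the other way, it is overstated. A later analysis plan cannot recover a pre-allocation score that was never collected.

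**Working it through.** **Step 1. Compare the two triggers.** Rule 1 is one parent's T0 completed; rule 2 is all T0 measurements completed.

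- One participating parent, T0 completed: the rules agree as far as parents are concerned.
- Two parents, both answering at the visit: the rules agree.
- Two parents, the second answering later: rule 1 allows randomisation and disclosure of the arm now; rule 2 makes the family wait.

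In the third case only rule 2 guarantees that the second parent's T0 precedes allocation. The case is foreseen, since later completion is permitted and a reminder is scheduled.

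**Step 2. Which analyses are exposed?** The primary model uses the adolescent's T1 PACS with the baseline PACS as covariate, and only adolescents complete the PACS. Their T0 is taken at the consent visit. No parent can complete T0 before that visit, so even under rule 1 the adolescent's score will in practice precede allocation, although rule 1 does not itself demand it. The exposed covariates are those of the parent secondary endpoints.

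The sample size is not affected. A two-sample t-test with difference 7, SD 11.4, two-sided alpha 0.05 and 80% power gives 42.6, so 43 per arm; 43 / 0.90 = 47.8, so 48 per arm and 96 families, as stated.

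**Step 3. Size of the bias.** Let b be the slope of outcome on baseline, f the fraction of intervention-arm parents who answer T0 after allocation, and s the shift in their answers in SD units, with no shift in the control arm. The observed baseline means then differ between arms by f × s for a reason unrelated to pre-existing differences. The adjusted estimate is the outcome difference minus b times the baseline difference, so

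bias ≈ −b × f × s.

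The documents give none of the three. The values below are assumptions.

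| f | s (SD) | b | bias (SD) |
|---|---|---|---|
| 0.10 | 0.2 | 0.5 | −0.010 |
| 0.10 | 0.5 | 0.7 | −0.035 |
| 0.25 | 0.5 | 0.6 | −0.075 |
| 0.50 | 0.2 | 0.5 | −0.050 |
| 0.50 | 0.5 | 0.7 | −0.175 |

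The ceiling of 0.50 for f follows from rule 1: with at most two parents per family and one T0 in before randomisation, no more than half of the enrolled parents can be late. A simulation of 400,000 records at f = 0.25, s = 0.5, b = 0.6 gave −0.073, against −0.075 from the formula. If control parents also answer late and react to their allocation, f × s is replaced by the difference of that product between arms.

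**The case against.** The best defence is that the two sentences are compatible: both state necessary conditions, and completion of everything includes completion by one parent. The opening sentence could define the minimum parent set, and the later one could refer to that set. This shows that the text is not a strict logical contradiction. It does not settle what happens with a late second parent: if every T0 is required, the opening sentence has no function, and if only the minimum set is required, the late T0 is allowed after disclosure.

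Four stronger readings are tempting, and the document does not support them:

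- **The primary result is biased.** It is not in practice, for the reason in step 2 of the working.
- **The bias is large.** A reader might multiply slope and shift alone, for example 0.7 × 0.5 = 0.35 SD. That applies only to the late respondents; the effect over all parents is scaled down by the late fraction, which is unknown. The shift and slope are assumptions too.
- **The oncologist's T0 is contaminated in the same way.** Intervention-arm oncologists cannot be blinded, but the article says that families are told the arm, and the oncologist's described part in the program comes after session 3. Nothing shows that oncologists know the arm within the reminder period.
- **Concealment is broken.** The section mentions both "using a concealed envelope method" and that "the randomization service will not release the randomization code". A service can prepare or hold envelopes, and no text says that data collectors hold the sequence. A conflict is not established.

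**Conclusion.** The point holds as a defect in the randomisation trigger that reaches the parent secondary endpoints. As written, the opening rule permits a second parent's T0 to follow disclosure of the arm and then to enter the model as a pre-randomisation score. This is a rule the article states, not a detail left to a fuller document.

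Its size is unknown. On the assumed ranges it runs from negligible (0.01 SD) to 0.175 SD, and the upper end needs every family to have two parents with the second one late, together with a shift of half an SD confined to the intervention arm. The correction is worth making because it is cheap, and because a pre-allocation score cannot be collected afterwards.

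**What to change.** **One trigger.** Replace the two statements with a single rule: allocation is released only when the adolescent's T0 and the T0 of every participating parent have been received, or recorded as missing after the one-week reminder. Record the date of each T0 and of allocation.

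**Families already randomised.** Compare the dates, and treat any parent score dated after allocation as a missing baseline. Those parents must stay in the model. With T1 as the outcome and baseline as a predictor, maximum likelihood does not recover a missing predictor, and the article plans no imputation by default, so they would otherwise drop out. Either impute the baseline from data collected before allocation, or use a missing-baseline indicator. Whether a score was in hand at allocation is fixed before allocation, so the indicator is a legitimate covariate. Add a sensitivity analysis that uses the late scores as recorded.

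**Oncologists.** Apply the same date check to their T0, but do not hold allocation for it.

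**Cost.** Protocol wording, a date check, up to one to two weeks' delay for some families, and slightly less precision for parents whose baseline is missing.
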